**Fig. 2 Fig2:**
[figure not shown]
Flow chart of the research design

### Data collection

Questionnaires assessing program targets (i.e., skills to deal with performance anxiety or social skills), specific goals of the skills-training programs (i.e., performance or social anxiety) and mental health (i.e., stress, internalizing and externalizing behavior, well-being and self-esteem) will be completed by students and parents prior to the start (T1) and after completion of the interventions in the experimental group (T2). Trainers complete questionnaires about program content (to assess program integrity) after each training session. Additionally, in a subsample of students (approximately *N* = 40 students per skills-training program), physiological parameters will be measured during a resting period to assess the basal stress levels of students (i.e., heart rate, heart rate variability and skin conductance measurements with wearables).

Student and parent characteristics (i.e., demographics including gender, age, ethnicity and education level, and expectations about the program) are assessed prior to the interventions, as well as trainer characteristics (i.e., demographics including gender, age, ethnicity, education level, and level of experience and perceived competence). Lastly, after completion of the intervention, students, parents and trainers will evaluate the skills-training program.

The design of this study has been approved by the Ethical Committee Psychology of Leiden University (CEP18–1105/419) and is registered in the Dutch Trial Register (number NL7438). To maintain participant confidentiality, all records that contain names or other personal identifiers will be stored separately from the collected data identified by code numbers.

### Study sample

For each school-based skills-training program we aim to include *N* = 130 students to ensure there is enough power for the analyses (*N* = 65 for both the experimental and waitlist control group). A total of *N* = 260 students will be included. This sample size is sufficient to investigate the effectiveness of the interventions and potential moderators, with a power of .80, an alpha of .05 and a medium effect size of .25 [63].

Participants are mixed-ethnicity students in the first, second, and third year of secondary schools (7th, 8th and 9th Grade students) of at least three schools in the Netherlands that offer education at various levels (from vocational education level to preparatory university education level). The students will be between 11 and 16 years old.

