## Methods/Design

### Design

A RCT will be conducted for both school-based skills-training programs targeting: 1) skills to deal with performance anxiety and 2) social skills. For each skills-training program, students who have indicated interest in attending a training at their school, will be randomized by the first author (stratified for education level) into the experimental group in which the training starts immediately or into a waitlist control group that receives the training approximately eight weeks later (see Fig. 2), using computerized randomization in a 1:1 ratio. We will use a multi-method (questionnaires and physiological data) and a multi-informant (students, parents and trainers) design and will recruit a mixed-ethnicity sample of students from different educational levels.

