## Discussion

This study protocol introduces the design of two RCTs investigating the effectiveness of school-based skills-training programs targeting skills to deal with performance anxiety or social skills to promote the mental health of adolescents. Further empirical tests of the utility of the RTI model will be published separately. Previous studies demonstrated reduced stress levels, reduced internalizing and externalizing behavior, increased self-esteem and improved well-being in adolescents receiving skills-training interventions. To overcome the limitations of previous studies, including study design (e.g., non-randomization, small sample sizes and the absence of moderator analyses) and use of mostly universal interventions, we will investigate small-group skills-training programs in a mixed-ethnicity community sample and use a RCT to exclude confounding (e.g., allocation and selection bias) as much as possible. We will use a multi-informant (i.e., students, parents and trainers) and multi-method (i.e., questionnaires and physiological measurements) approach. Furthermore, we will use a sufficiently large sample size to examine potential moderators of the effectiveness of the interventions (i.e., student, parent and program characteristics).

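### The .80 power claimed for moderators at N = 130 per programme holds only for one-degree-of-freedom interactions twice the size of the detectable main effect, and fails for several named moderators

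*Protocol article*

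**What the plan says.** The Study sample section sets 130 students per programme, "65 for both the experimental and waitlist control group", in order "to ensure there is enough power for the analyses". The parameters are power .80 with "an alpha of .05 and a medium effect size of .25". It applies them to two purposes at once: "This sample size is sufficient to investigate the effectiveness of the interventions and potential moderators, with a power of .80". The effect-size index is not named, and no separate effect size is given for moderation.

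Under Statistical analyses, each outcome is tested by ANCOVA on the post-test with the pre-test as covariate. Moderators, categorical or continuous, are added to the same models. The Background makes moderation the second aim and partly blames low power for the lack of earlier moderator evidence. The Discussion then offers size as an advance on earlier work: "we will use a sufficiently large sample size to examine potential moderators of the effectiveness of the interventions".

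The named moderators include ethnicity and educational level (Background) and basal stress. For basal stress, "physiological parameters will be measured during a resting period to assess the basal stress levels of students", but in a subsample of about 40 per programme (Data collection). Table 1 lists these measurements as both outcome and moderator.

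**The concern.** A sample size that suits a two-group comparison usually suits an interaction much less well, because the interaction is a difference between two differences. One effect-size figure covers both here, and the article does not say what it implies for a moderator.

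If the claim is taken at face value, a non-significant moderator test carries more weight than it should. A reader told that the trial had .80 power for moderators could take a null result as evidence of similar benefit across students, although a sizeable difference would often have been missed.

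**Working it through.** **Inputs from the article:** N = 130 per programme, 65 per arm, randomised 1:1; alpha .05; power .80; effect size .25; ANCOVA with the pre-test as covariate; about 40 students per programme in the physiological subsample.

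**Assumptions:** .25 is Cohen's f; each model has one covariate; there is no dropout and no clustering. SD means the residual SD of the ANCOVA unless stated otherwise.

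**Method:** noncentral F with noncentrality λ = N·f² and error degrees of freedom N − number of cells − 1.

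**1. Reproduce the plan's figure.** For two equal groups f = d/2, so f = .25 is d = 0.5.
- At N = 128, power is .801.
- At N = 130, λ = 130 × .0625 = 8.125 and power is .808.
- Reading .25 as Cohen's d instead would need 252 per arm, and 65 per arm would give power of about .30.

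So the f reading explains 130.

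**2. Two-level moderator, equal halves (four cells of 32.5).** Here f = difference in effects ÷ 4, so f = .25 is a difference of 4 × .25 = 1.0 SD.
- Power at f = .25 is .807.
- The smallest difference with .80 power is f = .248, or 0.99 SD. The smallest main effect is 0.495 SD. The ratio is 2.0.

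**3. Continuous moderator.** The standard error of the change in effect per moderator SD is 2/√130 = 0.175. The detectable change is (1.960 + 0.842) × 0.175 ≈ 0.49 SD per moderator SD, or about 0.98 SD between −1 and +1 SD.

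**4. The article's own f = .25 where the interaction is not 1 df in the full sample.**

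| Case | Power at f = .25 | N for .80 |
|---|---|---|
| 3 categories (2 df), N = 130 | .71 | 158 |
| 4 categories (3 df), N = 130 | .65 | 179 |
| Basal stress, N = 40, 1 df (λ = 40 × .0625 = 2.5) | .34 | 128 |

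The article does not state how many categories education or ethnicity will have; three and four are examples. At N = 40 the detectable difference between equal halves is about 1.8 SD.

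**5. Unequal subgroups.** With a proportion p in one subgroup, f = difference × √(p(1 − p)) ÷ 2. A 1.0 SD difference then gives:
- 30/70 split: f = .229, power .74
- 20/80 split: f = .200, power .62

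**6. Illustration of a smaller moderation.** Suppose the effect is 0.25 SD in one half and 0.75 SD in the other, a difference of 0.5 SD. This benchmark is chosen for illustration and is not in the article. Then f = .5/4 = .125, λ = 130 × .015625 = 2.03 and power is .29.

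If the 0.5 is on the raw scale, f becomes .125/√(1 − r²), where r is the pre-post correlation. The article gives no r.
- r = .5 (assumed): f = .144, power .37
- r = .7 (assumed): f = .175, power .51

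**The case against.** The strongest reply is that the sentence contains no false number. At f = .25 with one degree of freedom, power at N = 130 is .81 for the interaction as well as for the main effect. That is correct, so a reader who inferred a plain arithmetic error would be wrong. What stands against the claim is that it covers potential moderators without restriction, and at the same f it fails for multi-category moderators and for basal stress.

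A second reply is that the article states no expected size of moderation, so calling 1.0 SD too large, or 0.5 SD realistic, is a judgement. This also stands: the .29 is an illustration. The failures in step 4 do not depend on it, because they use the article's own f.

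Third, the 1.0 SD figure belongs to the residual scale and to equal halves, and many listed moderators are scale scores. On the raw scale with r of .5 to .7, the detectable difference falls to 0.86 to 0.71 SD. The detectable main effect falls in step, to 0.43 to 0.35 SD, so the two-to-one ratio between them remains.

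Fourth, Data collection openly calls the physiological group a subsample and claims no power for it. That is so, but Table 1 lists it as a moderator, and the Study sample sentence makes no exception for it.

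A reader might also infer that significant moderator findings will be mostly exaggerated or false. The documents do not support this: it would depend on how many true moderators exist and how large they are, and the article says neither.

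**Conclusion.** The concern holds in limited form. The sample size is sound for the main effect in each programme (.81 at d = 0.5). For moderators, the .80 statement is true only for a one-degree-of-freedom interaction in the full 130. There it means a 1.0 residual SD difference between equal subgroups, or about .49 SD of effect per SD of a continuous moderator. At the stated effect size it is not met with two or three interaction degrees of freedom (.71, .65) or for basal stress (.34). Nor is it met for a 1.0 SD difference when subgroups split 30/70 or 20/80 (.74, .62).

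This rests on reading .25 as Cohen's f and on the residual-SD scale. The category counts and splits are examples. Dropout or clustering in training groups is left out and would lower power further. The claim should be corrected because the second aim relies on it.

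**What to change.** In Study sample, name the effect-size index and confine the .80 power statement to the main effect in each programme. Add the moderation detectable with .80 power:
- about 1.0 residual SD between two equal subgroups;
- about .49 SD change in effect per SD of a continuous moderator;
- about 1.8 SD between equal subgroups in the physiological subsample of about 40.

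Note that multi-category moderators and unequal subgroups have less power. Change the Discussion sentence to match. Describe the moderator analyses as exploratory, and report each as an interaction estimate with a 95% confidence interval, so that a null result is read by its precision.

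No extra enrolment is needed. Pooling the two programmes is not advised: they are separate randomised trials with self-selected students, and pooling would assume common moderation. A check of that assumption at N = 260 (eight cells of 32.5, standard error √(8/32.5) = 0.50 SD) would detect only a difference of about 2.80 × 0.50 = 1.4 SD.

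The cost is a few sentences and a less favourable claim about what the trial can show on moderators.

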### Recruitment

#### Schools

So far, three Dutch urban secondary schools have been recruited. Possibly, additional schools will be recruited via the researchers’ contacts and networks. Schools that show interest will receive information about the study and will be asked to participate.

#### Participants

This study will be performed in the context of a Response to Intervention model (RTI) that aims to identify vulnerable students and provide them with appropriate interventions [64]. Before entering the current study, focusing on the effectiveness of school-based skills-training programs, classes of students receive educative information about stress and are asked about their own stress levels (i.e., Tier 1 of the RTI model: universal intervention targeting all students). After these three educative lessons, students will be asked to indicate if they would like to learn more about dealing with academic or social stress by following a skills-training program. Students will be asked to self-select to one of the school-based skills-training programs (i.e., skills to deal with performance anxiety or social skills), if needed assisted by parents or teachers (i.e., Tier 2 of the RTI model: targeted intervention directed at self-selected at-risk students). Students who self-select to a Tier 2 intervention are asked to participate in the current study.

The skills-training programs are offered by schools via their own care system or by external youth care organizations. The interventions are implemented at school by trained teachers or professionals. Students and parents receive written information about the different skills-training programs that are offered and receive an information letter about the corresponding research study. Trainers also receive an information letter about the study. Students and parents will be asked to provide active informed consent for the student’s participation in the study. If students or parents do not give consent to participate, the student will not receive the skills-training program offered by the study but will receive help via the schools’ own care system. Active informed consent will also be obtained from parents and trainers for their participation. After receiving consent, students will be randomized into the experimental condition or the waitlist condition. Figure 2 shows the flow chart of the design of the study.

### Interventions

Students in the experimental condition of each skills-training program will participate in seven 45-min small-group sessions during consecutive weeks. Weekly sessions will take place at the school of the students and the sessions will be delivered by an experienced trainer or trained teacher in small groups. The performance anxiety skills-training program consists of cognitive coping strategies (e.g., negative thought restructuring and managing emotions), relaxation techniques and dealing with pressure. The social skills training program consists of social skill building (e.g., identifying personal qualities, giving own opinions, setting boundaries, and standing up for yourself) and cognitive coping strategies (e.g., managing emotions).

### Waitlist-control group

The waitlist group will not receive any training during the implementation of the intervention in the experimental group and will only complete the pre-and post-intervention measurements. The waitlist group will receive the intervention immediately after the post-intervention measurements, approximately 8 weeks later than the experimental group.

### Instruments

Table 1 presents an overview of the measurements used at each assessment point for the skills-training programs.

**Table 1 Tab1:** Overview of the variables’ instruments and sources

Outcome	Variable name	Instrument	Time of measurement	Variable type	Source
Program targets	Coping skills	CERQ-short	T1, T2	Outcome	Students
	Social skills	SIG-A	T1, T2	Outcome	Students, parents
Direct program outcomes	Performance anxiety	PFAI, TAI	T1, T2	Outcome	Students, parents
	Social anxiety	RCADS, subscale social phobia	T1, T2	Outcome	Students, parents
Mental health outcomes	Stress levels	CSQ-CA	T1, T2	Outcome	Students, parents
	Internalizing and externalizing behavior	Y-OQ	T1, T2	Outcome	Students
	Well-being	WHO-5	T1, T2	Outcome	Students
	Self-esteem	RSES	T1, T2	Outcome	Students
Physiological stress response	Stress	Heart rate, heart rate variability, skin conductance	T1, T2	Outcome & moderator	Students
	Current stress and mood	VAMS	T1, T2	Outcome & moderator	Students
Demographics	Demographics	Developed for this study	T1	Moderator	Students, parents, trainers
Student characteristics	Social support	SSL-I	T1	Moderator	Students
	Perfectionism	CAPS-14	T1	Moderator	Students
	Stressful life events	Negative life events inventory	T2	Moderator	Students
	Perceived parental pressure	MIPS parental pressure subscale	T2	Moderator	Students
Program characteristics	Level of experience and competence of trainers	Developed for this study	T1	Moderator	Trainers
	Program integrity	Developed for this study	T2	Moderator	Trainers
	Treatment alliance	TASC	T2	Moderator	Students
Parent characteristics	Positive parenting behavior	VSOG subscale positive parenting	T1	Moderator	Parents

### Outcome measures

Program targets, direct program outcomes and mental health outcomes will be assessed before the start of the skills-training program and immediately after the completion of the program.

### Program targets

*Skills to deal with performance anxiety* will be measured with the Dutch version of the Cognitive Emotional Regulation Questionnaire – short form (CERQ-short) [65], completed by students. This instrument is a 18-item self-report measuring cognitive related coping (e.g., “I think I can learn something from the situation” or “I keep thinking about how terrible it is what I have experienced”). It consists of nine subscales: Self-blame, acceptance, rumination, positive refocusing, refocus on planning, positive reappraisal, putting into perspective, catastrophizing and other-blame. The authors made a distinction between maladaptive coping (self-blame, other-blame, rumination and catastrophizing) and adaptive coping (acceptance, refocus on planning, positive refocusing, positive reappraisal and putting into perspective) [66]. The internal consistency of the subscales is between .68 and .81 [65].

*Social skills* will be measured with the Scale for Interpersonal Behavior of Adolescents (SIG-A) [67, 68], completed by students and parents. For parents, an adapted version will be used where “I” is replaced with “my child”. The self-report version for students consists of 47 situations that are evaluated on two dimensions (i.e., how much anxiety students experience during these situations and how often they experience these specific situations). In this study we only use the performance dimension (i.e., frequency) to assess social skills. For example, the item “Starting a conversation with someone you haven’t met before” is scored on a scale from “never” to “always” for the performance dimension. The instrument consists of four subscales that refer to specific social situations: 1) display negative feelings (14 items, e.g., “If someone interrupts you, saying you find that annoying”) 2) express personal limitations (13 items, e.g., “Asking for an explanation about something that you didn’t understood”), 3) initiate assertiveness (9 items, e.g., “Starting a conversation with someone you haven’t met before”) and 4) display positive feelings (8 items, e.g., “Agreeing when someone makes a compliment about your appearance”). This instrument has sufficient psychometric properties with a Cronbach’s alpha above .80 for all subscales [68].

### Direct program outcomes

*Performance anxiety* will be measured by two instruments measuring different domains, i.e., fear of failure and test anxiety, completed by students and parents. For parents, adapted versions are used where “I” is replaced by “my child”. The short form of the Performance Failure Appraisal Inventory (PFAI) [69] will be used, translated into Dutch. The PFAI is a 5-item self-report instrument measuring fear of failure (e.g., “When I am failing, I am afraid that I might not have enough talent”) with good reliability (internal consistency between .72 and .82) [69, 70]. The Dutch short version of the widely used Spielberger Test Anxiety Inventory (TAI) [71, 72] will be used to assess anxiety in school testing situations. This instrument consists of 20 items (e.g., “I feel confident and relaxed while taking tests”) and has demonstrated adequate internal consistency (between .92 and .96) [73].

*Social anxiety* will be measured with the social phobia scale of the Dutch version of the Revised Child Anxiety and Depression Scale (RCADS) [74], completed by students and parents. For parents, an adapted version will be used where “I” is replaced with “my child”. This instrument consists of 9 items (e.g., “I worry what other people think of me”) and has good internal consistency (between .78 and .81) [74, 75].

### Mental health outcomes

*Stress levels* of students will be measured with the Chronic Stress Questionnaire for Children and Adolescents (CSQ-CA) [5] and will be completed by students and parents (adapted version). The CSQ-CA is a 19-item self-report questionnaire (e.g., “I often get upset about things that are not important”) that demonstrated good psychometric properties with an internal consistency of .87 [5]. In addition, physiological measurements are performed to assess basal stress levels in a subsample of students. Heart rate, heart rate variability and skin conductance are measured via a wearable (Shimmer3 GSR+; [76]) during a 5-min resting period where students watch a relaxing aquatic video [77]. Prior to the physiological assessment, students will complete Visual Analogue Mood Scales (VAMS) [78] about their current mood and stress level.

*Internalizing and externalizing problem behavior* will be assessed with the Youth Outcome Questionnaire (Y-OQ-30.1) [79], translated into Dutch and completed by students. This instrument consists of 30 items (e.g., “My emotions are strong and change quickly”) and measures change in psychological symptoms and social functioning. It includes six subscales: somatic complaints (3 items), social isolation (2 items), aggression (3 items), conduct problems (6 items), hyperactivity/distractibility (3 items) and depression/anxiety (6 items). Internalizing problem behavior will be assessed with the subscale depression/anxiety and externalizing problem behavior with the subscales aggression and conduct problems. The internal consistency of the total scale is .92 and between .55 and .85 for the different subscales [79].

*Well-being* of students will be assessed with the Dutch version of the WHO-Five Well-Being Index [80], which consists of 5 items (e.g., “My daily life has been filled with things that interest me”). This instrument has good internal consistency for an adolescent sample (between .82 and .85) [81, 82].

*Self-esteem* is reported by students by completing the Dutch version of the Rosenberg Self-Esteem Scale (RSES) [83, 84]. The instrument consists of 10 items (e.g., “I take a positive attitude toward myself”) and has sufficient internal consistency (between .77 and .88) for high school students [83].

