In sum, previous studies targeting skills to deal with performance anxiety and social skills in secondary school students demonstrated promising results, for academic and social stress as well as for mental health outcomes. However, previous research shows several limitations. First, only few studies performed a randomized controlled trial (RCT) [30, 35], which means that in non-randomized studies there might be confounding factors or bias. Second, only few studies used a targeted small-group intervention [28, 30, 35], which means that in studies with universal interventions there might be minimal or no effect for at-risk students because their greatest effect is on low-risk students, who are not the desired target [36]. Moreover, these studies had relatively small sample sizes (*N* = 74 and *N* = 56) [30, 35] which precludes clear conclusions about the effects, or targeted youth that experienced a traumatic event [28], precluding conclusions about non-clinical community samples. Third, only a few studies investigated mixed-samples of students from diverse ethnic backgrounds [30, 31, 33], which is important to be able to draw conclusions that generalize to the whole population [37]. Hence, there is still insufficient evidence for the effectiveness of skills-training programs, especially for students in mixed-ethnicity community samples. Additionally, little is known about potential moderators of the effectiveness of school-based skills training programs, likely due to power issues. Which students benefit from such training programs and which factors contribute to their effectiveness?

Moderators are student, parent and program characteristics that are likely to affect the effectiveness of the training programs. Student characteristics that may affect the effectiveness of the skills-training programs include demographic characteristics (i.e., age, gender, ethnicity, educational level and socioeconomic status (SES)) and social support, perfectionism, stressful life experiences, severity of problems, perceived parental pressure and basal stress levels.

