### Statistical analyses

To examine the effectiveness of the skills-training programs, the effects of all outcome measures will be investigated by conducting analyses of covariance (ANCOVAs). The dependent variables are the outcome measures at post-test (program targets, direct program outcomes and mental health outcomes), the independent variables are the conditions and the covariates are the pre-test (baseline) measurements of the outcome measures. The effect of potential categorical and continuous moderators on the effectiveness of the skills-training programs on the specific goals of the programs and mental health of students will be examined by adding the moderators to the ANCOVAs. Data will be imported from an online server software (i.e., Qualtrics) and will be securely stored at the server of Utrecht University where data back-ups will be performed regularly.

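### Moderation by basal stress rests on about 40 students per programme, so the statement that the sample suffices for moderators does not cover it; the all-student stress questionnaire has no explicit moderator role

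*Protocol article*

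**What the plan says.** All references are to the protocol article.

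- **Background** lists the student characteristics that may change the programmes' effect. The list ends with "severity of problems, perceived parental pressure and basal stress levels". Moderation of both programmes on all outcomes is the second aim.
- **Data collection** restricts the wearable recording, which is the source of the basal stress measure, to roughly 40 students in each programme. **Mental health outcomes** confirms the restriction: "physiological measurements are performed to assess basal stress levels in a subsample of students". The VAMS mood and stress rating is placed just before the recording.
- **Table 1** types heart rate, heart rate variability and skin conductance, and also the VAMS, as "Outcome & moderator". The row for the stress questionnaire reads "CSQ-CA T1, T2 Outcome Students, parents". It has no moderator role and no subsample limit. Its stated internal consistency is .87.
- **Study sample** plans 130 students per programme, 65 per arm. It calls this sufficient for effectiveness and for potential moderators, at power .80, alpha .05 and a medium effect size of .25. The Discussion repeats that the sample is large enough for moderators.
- **Statistical analyses** says that moderation "will be examined by adding the moderators to the ANCOVAs".

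**The concern.** The sufficiency statement covers potential moderators without exception, yet one named moderator is observed in under a third of the sample (40/130 = 30.8%). The Background suggests that power problems explain why so little is known about moderators. For basal stress, the plan repeats that limitation while stating that the sample is adequate. A non-significant interaction in about 40 students could then be read as evidence that basal stress does not matter, when the test had little chance of showing that it did.

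A related gap is that a T1 stress score planned for every student has no stated part in the moderator analyses. Stress is the protocol's route to reaching students, so whether those who report more of it at the start benefit differently is a natural question for the second aim. The data for a better-powered look at it are already planned.

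**Working it through.** **Inputs from the article.** N = 130 per programme, 1:1 allocation, alpha .05, power .80, effect size .25; physiology subsample about 40 per programme.

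**Assumptions.** The value .25 is Cohen's f; moderation is tested by a condition-by-moderator term with 1 df in an ANCOVA with 5 parameters; students are independent; arms are equal; nobody drops out; effects are in residual SD units.

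**Step 1: reproduce the planned N.** The test is a noncentral F with 1 numerator df and noncentrality λ = f² × N. With f = .25 and N = 130, λ = .0625 × 130 = 8.125 and power is .81. The smallest N that gives .80 is 128, so the stated 130 reproduces. Reading .25 as a standardised mean difference does not reproduce it: that would need 504 in total, and power with 65 per arm would be .30.

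**Step 2: the same interaction test at the two sample sizes** (denominator df = N − 5).

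| N | λ at f = .25 | Power at f = .25 | Smallest f at .80 power |
|---|---|---|---|
| 130 | 8.125 | .81 | .25 |
| 40 | 2.5 | .34 | .46 |

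Because 40 is approximate: power is .31 at 36 students and .37 at 44. Pooling both programmes' subsamples (N = 80) would give about .60.

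**Step 3: translate into differences in training effect.**

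- *Two equal halves (high against low on the moderator).* There are four cells of N/4, so SE = √(4/(N/4)) = √(16/N). That is 0.63 SD at N = 40 and 0.35 SD at N = 130. Since λ = (difference/SE)², f = difference/4. The difference detectable at .80 power is 4 × .456 = 1.82 SD at N = 40 and 4 × .248 = 0.99 SD at N = 130.
- *Continuous moderator, per SD.* SE = √(2/(N/2)) = √(4/N), which is 0.32 at N = 40 and 0.18 at N = 130. Here f = slope/2, so the detectable slope is 0.91 SD per SD at N = 40 and 0.50 at N = 130.
- *Ratio of standard errors.* √(130/40) = 1.80.

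**Step 4: a smaller interaction.** For a difference of 0.5 SD between halves, f = 0.5/4 = .125. Power is about .29 at N = 130 and .12 at N = 40.

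**The case against.** The strongest reply is that resting physiology and perceived chronic stress are different things, and that the article keeps them apart. Basal stress is consistently the resting recording. Table 1 gives the moderator role to that recording and to the VAMS taken at the same session. A reader might infer that the protocol picked a poor measure of the stress moderator over a good one, and that the CSQ-CA should replace the wearable. The documents do not support that. The CSQ-CA measures another construct and could only complement basal stress.

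Secondly, a reader might infer that baseline CSQ-CA is excluded from moderation. That also goes too far. The Background lists problem severity as a moderator, and Table 1 has no separate instrument for it, so T1 questionnaire scores may already be intended for that use. What can be said is that the CSQ-CA has no explicit moderator role.

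Thirdly, the article gives no specific rationale for basal stress as a moderator, so it should not be called central to the second aim on the documents' authority.

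Fourthly, the full sample is no cure. An interaction of f = .25 means about 1 SD between halves, twice the planned main effect (f = .25 is about 0.5 SD between arms), and Step 4 shows low power for anything modest.

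All four replies stand. None of them rescues the sufficiency statement for a moderator measured in about 40 students.

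**Conclusion.** The point holds in a limited form. For basal stress (resting physiology, with the VAMS from the same session) the claim of .80 power at f = .25 fails: power is about .34 and the smallest detectable f about .46. That the VAMS is confined to the same subsample is the natural reading of its placement before the recording, but it is not stated outright. The power figures rest on .25 being Cohen's f, a 1-df interaction, independent students and no dropout. Training is delivered in small groups, so independence is a simplification.

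The missing moderator role for the T1 CSQ-CA is a lost opportunity and not a contradiction. Using it would make the standard error about 1.8 times smaller, but would not make modest interactions detectable. The main effectiveness comparison is unaffected. The matter concerns the second aim and can be put right by wording.

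**What to change.** 1. **Study sample section (and the matching sentence in the Discussion):** limit the sufficiency statement to moderators measured in the full sample, and name the physiological measures and the VAMS as exceptions.
2. **Statistical analyses:** label moderation by heart rate, heart rate variability, skin conductance and the VAMS as exploratory. Report the number analysed and give the interaction as an estimate with a confidence interval.
3. **Table 1 and Statistical analyses:** type the T1 student CSQ-CA as both outcome and moderator, for example as a stated measure of the problem severity already listed in the Background. Test condition by centred T1 CSQ-CA in all randomised students of each programme. Report it as perceived chronic stress, separately from basal stress. Where the CSQ-CA is itself the outcome, its T1 score is already the covariate, so only the product term is added.

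**Cost.** The changes are to wording only, with no new data or visits. The price is one more interaction test per outcome in an already long set. The text should also admit that, at 130 students, .80 power is reached only for large interactions: about 1 SD between halves, or about 0.5 SD per SD of baseline stress.
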